**Methods:**

(Aim 1) At 7 sites in the Veterans Health Administration (VA), a mixed methods pre-implementation evaluation will identify determinants and their potential impact on uptake of EMPOWER and inform modifications to the intervention and implementation strategies as needed. (Aim 2) A staircase cluster randomized design will evaluate the rollout of the implementation strategies, beginning with Audit and Feedback (low-intensity) and then switching to Implementation Facilitation (high-intensity) after 6 months. Implementation Facilitation is hypothesized to have a greater impact on the reach, effectiveness, adoption, implementation (fidelity), and maintenance of EMPOWER. (Aim 3) A budget impact analysis will estimate the average cost of implementing EMPOWER at future sites and comparative costs for implementing the low- and high-intensity strategies.

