#### Design

We will conduct an adaptation of the multi-site hybrid type 3 cluster randomized staircase stepped-wedge trial, evaluating the implementation of EMPOWER while gathering data on its effectiveness. The staircase design is an adaptation to stepped wedge designs (SWD) that accommodate more flexible implementation (i.e., less burden to sites and clinicians). At the same time, it offers robust statistical efficiency given that statistical information is often strongest around time periods in the SWD when switching from one implementation strategy to another [44]. For EMPOWER, of interest is the effect of switching from Low Intensity (LI) to High Intensity (HI) implementation strategies. An imbalanced design [45] will be employed in which sites will spend twice as long in HI than LI (see Fig. 2). The use of an imbalanced design further accommodates the anticipated needs of sites to be enrolled in EMPOWER.

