#### Sample

At each implementation site, eligible patients will be identified from VA’s Homeless Registry “Hot Spot” reports, which use real-time data on acute care service utilization to identify high-need, housing-insecure patients [7, 46]. These reports identify veterans on the VA Homeless Registry (i.e., those who had received VA housing services in the past two years) who had ≥ 1 hospital admissions and/or ≥ 2 ED visits in the past quarter of the fiscal year [47]. Reports are housed on VA’s Support Services Center (VSSC) website with data primarily drawn from the Corporate Data Warehouse (CDW). Data for the reports are updated nightly and separate reports are generated for those who are (and are not) enrolled in VA primary care. From these reports, we will identify patients at each implementation site who are (a) currently enrolled in HUD-VASH, (b) have a mental health and/or SUD diagnosis, and (c) have not been engaged in either primary care or mental health during the quarter that they were flagged on the report. Approximately 585 patients across the target sites are estimated to be eligible to receive EMPOWER during the project period.

Power was assessed by testing a total of 448,560 plausible scenarios for a binomial outcome (e.g., patient reach) with the effect size (θ) of central interest being the mean difference in proportion of patients reached when moving from LI to HI. We assessed the necessary number of patients to achieve Power = 0.80 at α = 0.05, by including a random intercept for each cluster in the analyses (τ) is ∈ {0.01, 0.05, 0.10, 0.15} with θ ranging from 0.01 to 0.20 increase in number of patients reached and an autoregressive correlation of 0.7 between LI and HI implementation periods. Under a variety of plausible scenarios, we assessed power in relation to sample sizes ranging from a total N of 200–1000 patients (the plausible lower and upper limits, respectively, of patients eligible for EMPOWER). We observed Power = 0.80 to be achieved in sample size ranges between 227 and 278 patients.

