#### Outcome measurement

The RE-AIM framework [34] will be used evaluate the implementation of EMPOWER. Reach will be measured in terms of the number of patients who are willing to receive EMPOWER, out of all patients that are estimated to be eligible at potential sites. Effectiveness will be operationalized as number of outpatient visits in primary and specialty visits for mental health/SUD care, engagement in Whole Health services offered by sites [50], and premature exits from the HUD-VASH program. Additional patient-level outcomes will include rates of suicide screening and hospitalizations and emergency department visits, particularly for mental health or substance use. All service use variables will be measured in terms of receipt in VA and in the community using data from CDW. Adoption will be measured in terms of the number of peers in HUD-VASH at sites that are trained in EMPOWER and initiate the intervention with eligible patients at their site. Implementation will be operationalized in terms of fidelity to the various elements of EMPOWER at the site level, as measured via activity logs embedded in the EHR and electronic data capture logs (e.g., Qualtrics) to document type and length of encounters. Maintenance will be measured by the number of patients who are continuing to engage in EMPOWER and other VA services over the duration of the intervention (i.e., 6 months). To supplement the quantitative data used to operationalize the RE-AIM domains, we will conduct semi-structured qualitative interviews by phone with six key informants at each site – e.g., HUD-VASH peers, supervisors, and case managers (n = 36). The interview questions and format will be aligned with the qualitative data collection methods described above in Aim 1.

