Because Reach can be assessed as counts or rates of patients, we will specify Poisson GLMMs. For predicting individual reach to a veteran (a binary outcome), Poisson GLMMs with robust standard errors will be fit to allow convergence and provide accurate treatment estimates [52]. Because EMPOWER will afford more opportunity time in HI than LI to achieve outcomes, the Poisson GLMM approach allows a facile offset term to account for the different opportunity lengths for LI and HI conditions. At the patient level, time dynamics can be nuanced because care-seeking is dynamic and may represent residual confounding for which site-level randomization cannot account. Specifically, patients who seek more care may have a greater dosage of exposure to the condition the site is in at a particular time. Accordingly, we will also account for the longitudinal number of encounters (via stop codes) a patient has in the site and offset those encounter opportunities in the Poisson GLMM. This effort is aimed at improving precision of estimates of LI and HI effects in the models.

### Aim 3

To examine the implementation costs of EMPOWER, we will use a sequential mixed-methods design where an initial qualitative phase informs customization of the typical quantitative approach of a budget impact analysis [53]. Consistent with Eisman and colleagues’ work [54], we will conduct semi-structured interviews to identify stakeholder perspectives, which will guide the level of detail to be employed in micro-costing – e.g., including different payers’ relative priorities on how they may use cost information for implementation planning. We will use rapid qualitative methods, as described above in the Methods section for Aim 1. Interview participants will be drawn from a Learning Community of regional and national VA stakeholders associated with project and other medical center leadership.

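### If the Poisson offset for individual Reach is phase length, it biases the HI:LI ratio against HI and can reverse a true benefit

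*Protocol article*

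**What the plan says.** All references are to the Protocol article.

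- **Phase lengths.** Sites start in Audit and Feedback (LI), "then switching to Implementation Facilitation (high-intensity) after 6 months" (Abstract, Methods). The Design section adds that "sites will spend twice as long in HI than LI". HI is therefore 12 months by derivation; the article does not print that figure.
- **Scale of Reach.** Outcome measurement defines Reach as the "number of patients who are willing to receive EMPOWER, out of all patients that are estimated to be eligible at potential sites". The Sample section sets the effect size for power as "the mean difference in proportion of patients reached when moving from LI to HI". Both are proportions.
- **Model.** The Analysis section first allows Reach to be assessed as counts or rates. It then states: "For predicting individual reach to a veteran (a binary outcome), Poisson GLMMs with robust standard errors will be fit". The next sentence gives the longer time available under HI as its reason and says: "the Poisson GLMM approach allows a facile offset term to account for the different opportunity lengths for LI and HI conditions".

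The article does not say whether the offset is phase length, each patient's observed time, or the length of a data row. It does not confine the offset to counts, and it does not say that a veteran's time stops when the veteran is reached.

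**The concern.** An offset fixes the coefficient of log exposure at 1. That is right when the expected outcome grows in proportion to exposure, as a count of events from a steady inflow does. Binary Reach does not behave this way, for two reasons:

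- A veteran can be reached only once, so the probability flattens as time passes.
- If veterans become eligible continuously, a longer phase mainly adds veterans to the denominator. The proportion reached need not rise at all, and dividing by phase length then counts time twice.

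A phase-length offset is also constant within each condition, so it is completely aligned with the LI/HI indicator. The data cannot correct it, and neither can a site random intercept, because the shift lies within site. Equal performance would look like a disadvantage of HI, and a real advantage could be reported as harm. Reach is the outcome the article uses as its example for power.

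**Working it through.** **Inputs.** LI is 6 months (Abstract) and HI is twice LI (Design). θ runs from 0.01 to 0.20 and about 585 veterans are expected to be eligible (Sample). There are 7 sites. LI Reach is not stated, so every value of it below is an assumption. The article gives no figure for the offset model itself. Its power range of 227 to 278 patients cannot be checked without the LI proportion, and this point does not depend on it.

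**Step 1: what the offset does.** In a log-link model with offset log(6) for LI and log(12) for HI, the HI coefficient is

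log(p_HI / p_LI) − log(12/6) = log(p_HI / p_LI) − log 2.

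The reported ratio is (p_HI / p_LI)/2, so the hypothesis being tested becomes a risk ratio of 2. Only the 2:1 ratio of durations matters.

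**Step 2: no true difference, rolling entry, equal proportions.** The ratio is 1/2 = 0.50 at any level of Reach.

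**Step 3: no true difference, everyone at risk for the whole phase, equal constant hazards.** Twelve-month Reach is p12 = 1 − (1 − p6)². The reported ratio is (p12/12)/(p6/6) = (2p6 − p6²)/(2p6) = 1 − p6/2.

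| Assumed six-month LI Reach | Twelve-month HI Reach | Ratio with offset |
|---|---|---|
| 5% | 9.75% | 0.975 |
| 20% | 36% | 0.90 |
| 40% | 64% | 0.80 |
| 60% | 84% | 0.70 |

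**Step 4: reversal of a true benefit.** On the proportion scale, any p_HI below 2 × p_LI gives a ratio under 1. LI 40% against HI 60% (θ = 0.20, the top of the planned range) has a true ratio of 0.60/0.40 = 1.50 and is reported as 0.75. LI 20% against HI 30% is also reported as 0.75. On the hazard scale, the true hazard ratio at which the reported ratio equals 1 is log(1 − 2p6) / (2 log(1 − p6)). This is 1.06, 1.14, 1.28 and 1.58 at LI Reach of 10%, 20%, 30% and 40%. At 50% or more the reported ratio cannot exceed 1/(2p6) ≤ 1, whatever HI achieves.

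**Step 5: simulation.** Poisson model with robust standard errors, 585 veterans, 7 sites, LI:HI 1:2, site SD 0.3 on the log scale, 500 runs per scenario. Site effects were simulated but not fitted.

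| Scenario | Mean ratio | HI significantly worse |
|---|---|---|
| Equal proportions, 20% | 0.51 | 94% of runs |
| Equal proportions, 40% | 0.50 | 100% |
| 40% vs 60% | 0.75 | 81% |
| Equal hazards, LI Reach 40% | 0.79 | 68% |

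**Step 6: where an exposure offset works.** With each veteran's own time at risk, ending at reach, the simulated ratio was 0.985 to 1.021 under equal hazards and 1.27 to 1.32 when the true hazard ratio was 1.3. For site counts with a steady inflow of eligible veterans, the duration offset gave 1.00.

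**The case against.** The strongest reply is that the article never commits to this model. The paragraph opens with counts and rates, and says only that the Poisson approach allows an offset. The Analysis section describes an unbalanced panel in which veterans may be seen in LI, HI or both, which would also suit patient- or period-specific exposure. The analytic figure is not available here, and offset construction is often left to an analysis plan. The Sample section also words the effect as "θ ranging from 0.01 to 0.20 increase in number of patients reached", which sounds like a count, although values of 0.01 to 0.20 make sense only as proportions.

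Much of this stands. A reader might infer that the plan will certainly halve the risk ratio. The documents do not support that, because the form of the offset is not given and two other forms work (Step 6). What remains is that the offset sentence directly follows the binary model, gives unequal LI and HI time as its reason, and carries no restriction. Phase length is the most natural reading.

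A second reply is that time does need handling, and it is correct. If veterans are at risk for the whole phase, equal hazards give 40% against 64%, an unadjusted ratio of 0.64/0.40 = 1.6 in favour of HI. If the denominator is one fixed estimate of eligible veterans, numbers reached also accumulate with time. A reader might therefore infer wrongly that deleting the offset is enough.

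**Conclusion.** The point holds conditionally. If the offset is phase length and is applied to binary individual Reach, the HI:LI ratio is biased downwards. Under no true difference it is 0.50 with rolling entry and equal proportions, or 1 − p6/2 with whole-phase risk and equal constant hazards. Rolling entry has support in the Sample section, where eligibility rests on the past quarter's use and reports are refreshed nightly.

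The size depends on LI Reach, which the article does not state. Under equal hazards the bias is negligible when Reach is rare (0.975 at 5%) and large when it is common. The direction requires Reach to level off with time; a steeply rising hazard could offset or reverse it.

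Two further inferences go too far. Reach is the example outcome for power and is not declared primary, so this cannot be called a bias in the trial's primary result. Whether Reach should count willingness or receipt is a separate question of definition and has no part in this conclusion.

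**What to change.** State what the offset measures, and state that phase length will not be used as an offset for binary individual Reach. Replace it with one of the following:

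1. **Equal window.** Score Reach within the same fixed window from the Hot Spot flag in both conditions, with no duration offset.
2. **Person-month records.** Use one row per veteran per month from the flag until reached or end of observation, with the site's condition in that month and months since flag as covariates. Veterans who span LI and HI stay in the analysis.

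Do not remove the offset without adopting one of these. For site-level counts, use the log of the number of veterans actually flagged in that site-phase as the offset, or keep the duration offset only for counts with steady inflow.

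**Cost.** This is analysis work and wording; the design does not change. Flag dates come from the Hot Spot reports. The date on which a veteran counts as reached must also be recorded. An equal window of w months crosses the switch for w/6 of LI flags under steady inflow (1/6 = 17% at one month, 3/6 = 50% at three months; both windows are illustrations), and these must be censored or dropped. The person-month version avoids that loss.

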## Discussion

The hybrid type 3 trial described in this protocol paper will contribute to the broader literature on the promise and pitfalls of implementing interventions for vulnerable populations in healthcare settings in the US. Due to their multimorbidity and extensive social needs, HEVs are a particularly vulnerable patient population such that high-quality care often necessitates intensive, multicomponent interventions that can be costly to implement and sustain. Notably, the cost of care for HEVs is likely to increase in future years due to the aging nature of this population. That is, rates of homelessness in the US are expected to triple among those 65 years and older in the next decade [58]. Consistent with this, a recent analysis of a national cohort of high-need HEVs from the VA’s Homeless Hot Spot Registry found that the proportion of patients age ≥ 65 almost doubled from 2016 to 2022 (14% vs. 27%) [22]. An added complication to care efforts for this population is that many of these patients utilize community-based services, particularly acute care for psychiatric reasons [59], thus necessitating integration and coordination of care with VA services. For these reasons, knowledge about the relative impacts and relative costs of strategies aimed at implementing interventions such as EMPOWER for HEVs will be valuable for the larger healthcare system in the US.

The current trial will also provide valuable insights into the implementation of both peer-led and Whole Health-focused interventions more generally. Nationally, the peer workforce in the US has expanded considerably in recent years. For example, 77% of new staff positions in Certified Community Behavioral Health Clinics in 2024 were peers [60], and the majority of US states now reimburse for peer services through Medicaid [61]. However, high rates of burnout and turnover are well-documented challenges to implementation of this workforce [62], which often stems from inadequate training and supervision [62, 63]. For these reasons, Implementation Facilitation may be an ideal strategy to support implementation of new peer-led interventions, such as EMPOWER. The findings from the current trial will add to the small body of research on implementation of this workforce in large healthcare systems [32]. In terms of Whole Health care, health and wellness coaching, personal health planning, and various complementary and integrative therapies (e.g., acupuncture, meditation, yoga) have increased in the past decade [64]. As the US healthcare system continues to shift from a disease-centered model of care to one focused on supporting patients’ overall health and wellness [18], additional research is needed to understand what enables and hinders this model of care. The current trial in particular will provide novel insights into the impacts and costs associated with integrating peer support and Whole Health care.

One limitation of the current trial is the generalizability of findings to the implementation of EMPOWER and similar interventions outside the VA healthcare system. Though peers and other homeless program staff tasked with implementing EMPOWER may be familiar with the community-based services available to HEVs and will support linkage of these patients to those services as appropriate, the current trial is ultimately centered on the VA care system. In addition, though data on utilization of VA-paid services will be available for HEVs who receive EMPOWER in the current trial, community-based services that are not paid for by the VA will not be captured; thus, measurement of outpatient and inpatient care for HEVs may be an underestimate.

## Conclusion and impact

The current project will provide evidence of the impact and costs associated with using low- and high-intensity strategies to implement EMPOWER – a multi-component intervention for HEVs grounded in the evidence-based practices of peer support, patient-centered care, and Whole Health. By focusing on increasing care engagement in HEVs, EMPOWER can offer a high-quality care model for a large population of HEVs in the US. Accordingly, the findings will provide guidance to VA and other healthcare systems that frequently serve this high-need and vulnerable patient population.

## Data Availability

The datasets generated and/or analyzed during the current project will not be publicly available but will be available from the corresponding author on reasonable request.

## Abbreviations

ACORN: Assessing Circumstances & Offering Resources for Needs
BIA: Budget Impact Analysis
CDW: Corporate Data Warehouse
CFIR: Consolidated Framework for Implementation Research
DSR: Dynamic Sustainability Framework
EHR: Electronic Health Record
EBP: Evidence-based practices
EMPOWER: Employing Peer Outreach and Whole Health in Recovery
GLMM: Generalized Linear Mixed Effects Models
HEV: Homelessness-experienced veterans
HI: High Intensity
HUD: Housing and Urban Development
LI: Low Intensity
PARRQA: Planning for and Assessing Rigor in Rapid Qualitative Analysis
RCT: Randomized Control Trial
RE-AIM: Reach, Effectiveness, Adoption, Implementation, and Maintenance
SUD: Substance Use Disorder
SWD: Stepped Wedge Designs
VA: Veterans Health Administration
VASH: VA Supportive Housing
VSSC: VA Support Services Center
